#### Subgroup analyses

The intervention effect will be estimated with 95% confidence intervals for each trial nurse separately. A formal test of whether the intervention effect varies significantly by nurse will be assessed either by using an interaction of nurse by intervention in a linear regression model, or, if the assumptions are not met, by using a chi-squared test of heterogeneity in a standard meta-analysis of the nurse intervention effects, using estimates and standard errors obtained using the bootstrap method for each nurse. For ease of interpretation, the simpler interaction test will be presented if results are not materially different. The three other subgroup variables are study centre, total daily NRT prescribed (20 mg, 27 mg, 26 mg, and 33 mg) and daily top up amount prescribed (Enhanced oral NRT, Standard oral NRT). Subgroup analyses will be confined to analysis of the primary outcome and will use the same interaction analysis framework.

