### Genetic testing

All participants will give a sample of either blood or saliva for genotyping, although the results are only used for tailoring dose of oral NRT and communicated to participants in the intervention group.

This trial tests for variants in the mu-opioid receptor gene, *OPRM1*. It is expected that about 75% will be homozygous for Asn40, with about 25% heterozygous or homozygous for Asp40 (i.e. need the higher dose of NRT) [18]. DNA will be extracted from blood using commercially available methods. From participants who do not want to have a blood test, DNA will be extracted from saliva. Briefly, DNA is extracted using a standard "salting out" technique [30]. For the genotyping of the *OPRM1 *A118G polymorphism, PCR is carried out using an allele specific, two-tube primer method. The reaction mixture contained 0.5 μM of each *OPRM1 *and control primer, approximately 150 ng of DNA, 200 μM dNTPs, 2 mM MgCl_2 _and 0.5 units of Taq polymerase in a final volume of 25 μl. After an initial denaturation step for 10 min at 95°C, thermocycling consisting of 30 cycles of 95°C for 20 sec, 68°C for 45 sec, 72°C for 30 sec. A final extension phase of 72°C is followed by cooling of samples to 4°C. PCR products are separated on a 1% agarose gel at 200 V for 30 min and visualised using ethidium bromide. In order for samples to be valid, a 750 bp control product has to be formed in both allele specific reactions. A homozygote is indicated by the presence of a 561 bp product in one of the reactions and a heterozygote is represented by a 561 bp product in both of the reactions.

A greater than 95% success rate is expected for the extraction and amplification of DNA. In the event that DNA is not collected or laboratory procedures fail to extract and amplify the DNA from the sample, the participant will be asked to provide a further sample.

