### Trial medication

The trial will take place in the context of NHS stop smoking services, which provide behavioural support and medication to assist smoking cessation. At the time that this trial started, more than 70% of smokers in these clinics used nicotine replacement therapy (NRT) [28]. Current best practice is to use NRT in combination with behavioural support [31,32]. Smokers in the current trial will all be prescribed NRT patches plus oral NRT 'top-up' medication, which is approximately 35% more effective than NRT patch alone [33]. NRT patch dose will be tailored in the same way in both arms of the trial, namely according to how many cigarettes are smoked per day. Oral NRT dose will be determined on a different basis in each arm of the trial: those in the genotype arm will have the dose tailored according to the *OPRM1 *variant that they carry; those in the phenotype arm will have the dose tailored according to their nicotine dependence. Details of the basis for these prescriptions are presented below. The aim of treatment is to continue with full dose NRT for the first four weeks after the quit day, after which medication is reduced, according to patient need.

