##### i. Genotype arm (Intervention)

Participants will be informed that their oral dose of NRT is based on their genetic test result, using the following script:

*"Your extra NRT is based on the results of a genetic test. We did a genetic test on the blood sample that you gave last week. People have different versions of the 'OPRM1' gene. This gene influences how dependent you are on nicotine. There is more information on genes in the leaflet. Based on the results of your genetic test, you are more likely to be successful in stopping smoking if you have a (**standard dose/higher dose**) of extra NRT. Recent research shows that people with your genetic test result are more successful at stopping smoking if they take all of the extra NRT, as well as using their patch*.

You should wear a new patch for 24 hours each day for at least four weeks. The patch works by releasing a steady dose of nicotine into your blood stream. You have also been given a **(dose/high dose) **of extra NRT. Please use this as well as wearing the patch. You may wish to take it when you get a craving, but you can also take it at other times of the day. Even if you feel you don't need the extra NRT, you should take it. Many quit attempts fail because people don't take enough NRT or stop taking it before they have beaten their withdrawal symptoms. Remember that this dose has been calculated to suit your individual needs - try to stick to this amount each day in addition to wearing the patch."

Participants with the Asn variant will be advised to take additional NRT equivalent to the delivery of 6 mg of NRT a day. Those with the Asp variant will be advised to take additional NRT equivalent to delivery of 12 mg a day. A rationale booklet will be given to each participant describing:

i. their personalised additional oral dose of NRT based on their genetic test result. Participants with the Asn variant will be informed that they need a standard dose of additional NRT and participants with the Asp variant will be informed that they need a higher dose of additional NRT;

ii. the basis upon which this dose was calculated (*ie *a genetic test to establish which version of the "*OPRM1*" gene they carry);

iii. information about genes;

iv. information about the amount of additional NRT they should take in addition to wearing a new patch every day for at least 4 weeks;

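### The two subgroup analyses by prescribed NRT dose are not randomised comparisons, because the oral dose is set after randomisation by a different rule in each arm

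*Protocol article*

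**What the plan says.** The Subgroup analyses section names four variables for the primary outcome. Nurse is treated first. Of the rest it says: "The three other subgroup variables are study centre, total daily NRT prescribed (20 mg, 27 mg, 26 mg, and 33 mg". The last variable on its list is the oral amount alone, split into two levels: "daily top up amount prescribed (Enhanced oral NRT, Standard oral NRT". All of them "will use the same interaction analysis framework", that is, a test of subgroup by arm. No covariates are mentioned.

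Trial medication states: "Oral NRT dose will be determined on a different basis in each arm of the trial". In the genotype arm, "Those with the Asp variant will be advised to take additional NRT equivalent to delivery of 12 mg a day", and participants with the Asn variant are assigned 6 mg. In contrast, "those in the phenotype arm will have the dose tailored according to their nicotine dependence", with the FTND score deciding between the same two amounts. The patch rule is common to both arms and depends on cigarettes per day.

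On timing, the Consent process section places randomisation after the first clinic and a confirming telephone call. Data collection places the prescription at the second clinic. On data, Genetic testing says: "All participants will give a sample of either blood or saliva for genotyping". The FTND score and cigarettes per day are randomisation stratifiers.

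**The concern.** A subgroup-by-arm interaction can be read as effect modification when the subgroup is fixed before allocation and defined identically in both arms. Prescribed oral dose is neither. The Enhanced group consists of Asp carriers of any dependence in one arm and of highly dependent smokers of any genotype in the other. The Standard group consists of Asn homozygotes in one arm and less dependent smokers in the other.

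If dependence or genotype is related to adherence, the arms differ within a dose level before the information given to participants has any effect. The reported interaction could then suggest that genetic information works better or worse at the higher dose when it does not, or could hide a difference that exists. Dependence could plausibly matter through the outcome definition: a day with no NRT consumed, for example after resuming smoking, scores 0%, and non-attenders who report a return to smoking score zero for the rest of the 28 days.

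**Working it through.** **Inputs.**
- Asp40 carriers: about 25% (Genetic testing). Call this q.
- High FTND: about 25% at the initial cut-off of 7 (Phenotype arm). Call this pH.
- 315 per arm; 50% and 65% high users in the two arms, the rest uniform; within-group standard error 1.85% (Sample size calculation).
- Interim counts on the higher oral dose among the first 160 participants: 32 phenotype, 14 genotype.
- Assumptions, not in the document: FTND and genotype are independent; their effects b and g on mean adherence are additive; the true arm effect d is constant.

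**The plan's own figures.** The document gives none for the interaction. The SD can be taken from the sample-size model. Reading high use as 100%, the means are 0.50 + 0.50/2 = 0.750 and 0.65 + 0.35/2 = 0.825, which reproduces the stated 7.5-point difference. The SDs are 0.323 and 0.293, pooled 0.308, rounded here to 0.31. The stated standard error, read as per arm, implies 0.0185 × √315 = 0.328.

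**Which subgroups are affected.** The four daily totals are 14 + 6 = 20, 21 + 6 = 27, 14 + 12 = 26 and 21 + 12 = 33 mg. The patch part follows the same rule in both arms, so only the oral part causes the problem. It does so in both dose-defined variables.

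**Composition (share with high FTND, at 25% and independence).**

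| Subgroup | Genotype arm | Phenotype arm |
|---|---|---|
| Enhanced | about 25% | 100% |
| Standard | about 25% | 0% |

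For Asp carriage the pattern is reversed: 100% and 0% in the genotype arm, about 25% in both rows of the phenotype arm.

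**Expected contrasts, genotype minus phenotype.**
- Enhanced: (d + b·pH + g) − (b + g·q) = d − b(1 − pH) + g(1 − q)
- Standard: (d + b·pH) − (g·q) = d + b·pH − g·q
- Interaction (Enhanced minus Standard): **g − b**

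The prevalences cancel. Moving the FTND cut-off from 7 to 8 to balance the number of higher doses therefore changes subgroup sizes but does not remove this term.

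**Example.** Take b = −7.5 points, g = 0, d = 0, pH = 0.25. Enhanced = 7.5 × 0.75 = +5.6 points; Standard = −7.5 × 0.25 = −1.9 points; interaction = 7.5 points. Simulation gave +5.8, −1.8 and 7.6.

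**False-positive rate.** The interaction standard error is 0.31 × √(2/78.75 + 2/236.25) = 0.057. The normal approximation from this is shown beside 3,000-run simulations of the linear interaction model, two-sided 5%, g = 0.

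| b (points) | Simulated | Approximation |
|---|---|---|
| 0 | 5% | 5% |
| −5 | 15% | 14% |
| −7.5 | 25% | 26% |
| −10 | 42% | 42% |
| −15 | 74% | 75% |

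With SD 0.328 the approximation for −5 and −10 points is 13% and 38%.

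**Other cases simulated.**
- Dose shares as at the interim (32/80 = 40% and 14/80 = 17.5%, assuming 80 per arm), b = −7.5: interaction 7.6 points, rejection 26%.
- b = g = −7.5: the bias cancels, rejection 5%.
- A pure effect of dose on adherence, equal in both arms: no bias in the dose-subgroup interaction, rejection 5%.
- Subgroups defined by baseline FTND or genotype, no dose effect: rejection about 4% to 6%.
- The same baseline subgroups when the larger dose lowers adherence by 7.5 points: FTND interaction about 7.5 points; rejection about 25% to 27% for either factor.

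**The case against.** **These are supporting analyses.** That stands. The primary comparison uses everyone randomised and does not condition on dose. Nurse and study centre are unaffected too. A reader might infer that the trial's main result is compromised; nothing here supports that.

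**The authors saw the issue.** Design considerations accepts that the outcome is open to differential prescribing and promises to analyse genotype and recorded phenotype in both arms, to judge how far differences between arms could be attributed to either. This supplies the raw material for a repair, but is not tied to the dose subgroups, which remain defined by prescribed dose. An unseen analysis plan might add covariates. The protocol nevertheless positively names these variables and this test.

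**Confounding is partial.** This stands. A reader might infer that dose is fully confounded with dependence. In the genotype arm dose does not depend on FTND, and its Enhanced group still contains highly dependent smokers.

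**The bias is conditional.** Also correct. A reader might infer that a false interaction is certain, or equals the effect of dependence alone. The bias is g − b, so it is zero if neither factor matters or both matter equally. Even at b = −10 points, most simulated runs did not reject. Nor should an interaction be measured against the 7.5% target, which is a main effect and not a difference of differences.

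**Baseline subgroups have their own weakness.** They pick up any effect of dose itself, whereas dose-defined subgroups do not. Design considerations worries about just such an effect. This is a reason to report the limitation, and possibly to keep a descriptive dose analysis, but not to present the dose interaction as a randomised one.

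**Conclusion.** The point holds for the two dose-defined subgroup variables. Their within-dose arm contrasts are not protected by randomisation, and the interaction test targets the true effect modification plus g − b. Balancing the number of higher doses does not correct this.

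The size is unknown because the document gives no effect of FTND or OPRM1 on adherence. Over an assumed range of −5 to −10 points for high FTND, with no genotype effect, SD 0.31 and 315 per arm, a true null interaction is rejected in about 15% to 42% of runs. The result that prevalences cancel rests on independence of genotype and FTND and on additive effects. The 40% interim share should not be carried forward as the high-FTND share for the whole trial, since it belongs to the cut-off that was replaced and assumes 80 per arm.

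This is a specific, easily corrected fault in secondary analyses. It does not threaten Hypothesis I.

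**What to change.** In Subgroup analyses:

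1. Make the pre-specified factors baseline ones known in both arms: FTND stratum, OPRM1 genotype and cigarettes-per-day stratum. Because the FTND cut-off changed during recruitment, state one definition for the analysis, or use the score.
2. If "total daily NRT prescribed (20 mg, 27 mg, 26 mg, and 33 mg" and the top-up amount are kept, adjust for FTND and genotype in both arms, and label the results non-randomised and descriptive.
3. Optionally, show the cells in which genotype and FTND imply the same oral dose, where prescribing is equal between arms. At 25% × 25% the both-high cell is about 0.0625 × 630 = 39 people, roughly 20 per arm, too few for firm conclusions. The both-low cell is about 0.5625 × 630 = 354, roughly 177 per arm.
4. State when interpreting the FTND and genotype subgroups that they also reflect any effect of dose on adherence.

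The cost is rewording and a few extra models. FTND and cigarettes per day are already stratifiers, and DNA is collected from everyone. A participant whose sample fails would have no genotype; the protocol expects extraction and amplification to succeed in more than 95% and provides for a repeat sample.

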#### Handling missing data in the primary outcome

Analysis of adherence over the 28-day period will be primarily on an intention to treat basis, involving all randomised participants. If clinic non-attenders report returning to smoking or cannot be contacted by the nurse to establish adherence, then adherence will be counted as zero for the remaining 28 day period. Missing daily adherence data from those participants who attended the clinic session will be imputed from the average taken from the days that are not missing. This analysis will be supported first by an explanatory per protocol analysis which excludes those participants not receiving the intervention, and second, by a sensitivity analysis.

### Design considerations

This is the first clinical trial evaluating the behavioural impact on adherence of prescribing medication using genetic rather than phenotypic information. There are some specific issues in choice of design for trials of interventions of this kind.

Our research questions ideally required us to randomise the information concerning the basis for prescribing (i.e. telling the two groups that their prescriptions depended on gene or nicotine dependence) and to hold the NRT treatment constant across both groups. This design was the most attractive experimentally, but unacceptable on the grounds that it would have required us to deceive participants about the true basis for their prescriptions. We considered seeking informed consent to this approach, but rejected it because of concerns that this might undermine trust in the trial as a whole.

We therefore required a design which would result in a balance of gene variants and nicotine dependence across groups and would generate similar prescription of NRT in both groups, despite the basis of prescription (genotype or phenotype) varying systematically by group. If by chance or systematic effect a greater dose of NRT was prescribed in one group than the other, then any apparent intervention effect on abstinence might be due to more effective prescribing rather than to differing expectations of effect of adherence.

We selected the design of an open-label, parallel group randomised trial in which participants were randomly allocated to one of two groups: oral NRT prescribing tailored by DNA analysis, or oral NRT prescribing tailored by nicotine dependence. We have monitored prescriptions across the groups for the need for a pre-determined change in threshold for definition of heavy smoking in the phenotype group to assure prescribing balance with the genotype group. We defined adherence to NRT rather than abstinence from smoking as our primary outcome, and adherence was defined in terms of the proportion of NRT prescribed that was consumed. This outcome is still open to the impact of differential prescribing across groups as participants might systematically consume less of a larger dose. We will analyse genotype and recorded phenotype in both trial groups thereby allowing analysis to indicate the extent to which any differences between arms could be attributed to differences in genotype or phenotype.

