Planned interim analysis (overseen by the Trial Steering Committee) including the first 160 participants revealed a substantial difference between the number of participants that obtained the higher dose of additional NRT in the phenotype arm (n = 32) compared to the genotype arm (n = 14). In order to balance the higher and lower dose oral NRT in the two arms, a cut-off of 8 rather than 7 on the FTND will be used for the remainder of recruitment.

A rationale booklet will be given to each participant, describing:

i. their personalised additional oral dose of NRT based on their questionnaire responses. Participants who score less than 8 (or 7, prior to an interim analysis) on the FTND are informed that they need a standard dose of additional NRT; participants who score above the cut-off are informed that they need a higher dose of additional NRT;

ii. the basis upon which this dose was calculated (*i.e. *responses to a questionnaire, revealing how dependent they are on nicotine);

iii. information about the amount of personalised additional NRT they should take in addition to wearing a new patch every day for at least 4 weeks;

iv. the physiological mechanisms by which wearing their NRT patch and taking all their personalised dose of additional NRT each day for four weeks increases their chances of stopping smoking.

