### Outcomes

#### Hypothesis I

##### i) Primary outcome

The primary outcome is adherence to a 28-day prescription expressed as the proportion of all NRT prescribed (in milligrams) that is consumed each day in the first four weeks of quitting, averaged over the four week quit period.

The proportion consumed will be measured by self-report daily diary, backed up by pill counts. If pill counts are discrepant with the diary, this will be discussed and reconciled by the research nurse at the weekly clinic visit. The adherence proportion on any day is the ratio of the amount of NRT consumed to the amount prescribed. The denominator of the amount prescribed derives from both NRT patch and top up. For example, for someone prescribed 1 × 21 mg patch and 6 × 1 mg oral NRT doses (equivalent to 6 × 2 mg gums, for example), the denominator is 27 mg. Consumption of the prescribed top ups and any additional top ups taken will count towards the total NRT consumed on a day. Wearing the patch for 24 hours a day will count as the maximum amount of NRT mg prescribed as having been consumed from the patch. If the patch is worn for a fraction of the 24 hours (such as 12 hours) then this fraction of the total NRT mg from the patch will be counted as having been consumed (such as 0.5 × 21 mg for a 21 mg patch worn for 12 hours), pro-rata. If the patch is not worn for 24 hours a day but additional oral NRT is taken then this will count towards the total NRT consumed on that day. For example, if someone prescribed a 21 mg patch and 6 mg of oral NRT, wears their patch for 16 hours a day and uses an additional 7 pieces of gum to make up for the 7 mg of NRT lost by the patch coming off early, this will be treated as 100% adherence (i.e. they have consumed 14 + 6 +7 = 27 mg). NRT consumed above that prescribed on any day could occur through excess top up consumption and will be treated as a daily proportion of 100%. The daily proportion will be treated as 0% when no NRT is consumed, if, for example, a person has resumed smoking.

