### Sample size calculation

With 315 participants per arm, there is 90% power to detect a 7.5% difference in the mean proportion of NRT consumed using a two-tailed test at the 5% level of significance. This is equivalent to detecting approximately a two days' worth difference in mean NRT consumption over a 28-day period. The calculation is based on the skewed distribution of days of prescribed NRT patch use reported by Alterman and colleagues [41] where 55% of participants reported high use and the remainder had a uniformly spread distribution of use. Assuming the same mixed distribution, with 50% and 65% of high-use participants and the remainder uniformly distributed in the two arms, the implied difference in mean consumption was 7.5%. By repeated random sampling, the distribution of the mean within each group was close to normal. The estimated pooled within-group standard error was 1.85%, and both Mann-Whitney and unpaired t-tests provided at least 90% power.

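### The primary adherence outcome is open to bias from unequal oral dosing between arms, and the genotype/phenotype analysis offered in response, as worded, would not remove it

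*Protocol article*

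**What the plan says.** The following parts of the Protocol article bear on this point.

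- **Outcomes, primary outcome.** Adherence on each day is milligrams consumed over milligrams prescribed. "The denominator of the amount prescribed derives from both NRT patch and top up". A day is capped at 100% and scores 0% when no NRT is taken.
- **Oral NRT prescription.** The oral dose follows the *OPRM1* variant in the genotype arm and the FTND score in the phenotype arm. Among the first 160 participants there was a substantial difference in the number given the "higher dose of additional NRT in the phenotype arm (n = 32) compared to the genotype arm (n = 14"). The FTND cut-off was then moved from 7 to 8 for the rest of recruitment.
- **Randomisation, Method.** FTND category is a stratification factor.
- **Statistical Analysis.** The primary comparison is an independent-samples t-test, confirmed by a bootstrap interval. No dose term is stated. Subgroup analyses of the primary outcome are planned by total daily NRT prescribed (20, 26, 27 or 33 mg) and by top-up amount.
- **Design considerations.** Holding treatment constant across arms was the ideal, but was rejected because it would have meant deceiving participants. The text concedes: "This outcome is still open to the impact of differential prescribing across groups as participants might systematically consume less of a larger dose". Its answer is to analyse genotype and recorded phenotype in both groups, "allowing analysis to indicate the extent to which any differences between arms could be attributed to differences in genotype or phenotype".

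**The concern.** The trial asks what the information about the basis of the prescription does to adherence, with the prescription itself similar in both arms. Because prescribed dose is the denominator, a person who takes the same milligrams scores lower on the higher dose. If one arm has more higher-dose participants, part of the between-arm difference can come from the denominator and not from the information.

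The plan recognises this, but the remedy it names looks at the wrong quantity. Genotype is balanced by randomisation in expectation, and FTND category by stratification as well. What differs between arms is the rule that turns those characteristics into a dose. A reader who took the genotype/phenotype analysis as reassurance about dose would be relying on something it does not provide.

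**Working it through.** **1. The benchmark.** Under Sample size calculation: "With 315 participants per arm, there is 90% power to detect a 7.5% difference in the mean proportion of NRT consumed". The test is two-sided at 5%, and the assumed distributions are described as "with 50% and 65% of high-use participants and the remainder uniformly distributed in the two arms". Taking high use as 100% and the rest as uniform on 0 to 100%, the mean is p + (1 − p)/2. This gives 75.0% for p = 0.50 and 82.5% for p = 0.65, so the 7.5-point difference is reproduced. The pooled SD is 30.8%. The standard error per arm is 30.8/√315 = 1.74% (stated: 1.85%), and that of the difference is 30.8 × √(2/315) = 2.46 points. This mixture gives 86% power for the two-sided t-test, not 90%. That is a separate matter and does not affect what follows.

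**2. Penalty per higher-dose participant, 21 mg patch (27 or 33 mg prescribed), full patch wear**

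| Oral intake | Standard dose | Higher dose | Penalty (points) |
|---|---|---|---|
| None on either dose | 21/27 = 77.8% | 21/33 = 63.6% | 14.1 |
| 6 mg on either dose | 27/27 = 100% | 27/33 = 81.8% | 18.2 |
| 6 mg, plus half of the extra 6 mg on the higher dose | 100% | 30/33 = 90.9% | 9.1 |
| All of the prescribed dose | 100% | 100% | 0 |

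With a 14 mg patch (20 or 26 mg), 6 mg on either dose gives a penalty of 1 − 20/26 = 23.1 points.

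**3. Imbalance.** The interim arm sizes are not given. Assuming 80 each, 32/80 − 14/80 = 40.0% − 17.5% = 22.5 points. With splits of 75/85 or 85/75 (phenotype/genotype) it is 26.2 or 19.0. If everyone recruited later is balanced, the trial-wide imbalance is 18/315 = 5.7 points.

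**4. Bias = imbalance × penalty**

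| Intake assumption | First 160 | Trial-wide, later recruitment balanced |
|---|---|---|
| In proportion to dose | 0 | 0 |
| Half of the extra taken (21 mg patch) | 2.0 | 0.5 |
| Same milligrams, 21 mg patch | 3.2 to 4.1 | 0.8 to 1.0 |
| 6 mg on either dose, 14 mg patch | 5.2 | 1.3 |

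With a standard error of 2.46 points, a 1.0-point bias raises the two-sided 5% error rate to about 7%. A 4.1-point bias would raise it to about 38%, but only if the interim imbalance ran through the whole trial.

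The direction after the cut-off change is unknown. If the later shares were, say, 12% phenotype and 17.5% genotype, the bias among those participants would be −5.5% × 14.1 to 18.2 = −0.8 to −1.0 points. For the whole trial to reverse, the later overshoot must exceed 18/235 = 7.7 points.

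**5. Why adjusting for genotype and FTND leaves the bias.** Let g be the share of Asp carriers and f the share above the FTND cut-off, each equal in the two arms by randomisation. The arms receive different doses in only two cells:

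- Asn with high FTND: higher dose in the phenotype arm only.
- Asp with low FTND: higher dose in the genotype arm only.

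The net imbalance over cells is P(Asn, high FTND) − P(Asp, low FTND) = f − g, whether or not the two are independent. With g = 0.175 and f = 0.40, taken as independent: 0.825 × 0.40 − 0.175 × 0.60 = 0.330 − 0.105 = 0.225. That is the full imbalance again, so averaging over the covariates does not shrink it.

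A simulation agrees (630 participants, no true arm effect, same milligrams taken on either dose, interim imbalance kept throughout). The bias was +3.2 points unadjusted, +3.2 adjusted for genotype and FTND, and about 0 (−0.1) among participants with the same dose under both arms.

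**6. The dose subgroups.** Within a prescribed-dose stratum the denominator is equal, but the higher-dose stratum sets Asp carriers in one arm against high-FTND smokers in the other. When high dependence itself lowered consumption by 10%, the simulated within-dose comparison was off by about −1 point with no true effect. The same-dose comparison was off by +0.1.

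**7. Size of the same-dose subset.** Its share is (1 − g)(1 − f) + gf, assuming independence. For g = 0.25, f = 0.40 it is 0.45 + 0.10 = 0.55. For g = f = 0.175 it is 0.68 + 0.03 = 0.71. The standard error grows by 1/√0.71 = 1.19 to 1/√0.55 = 1.35. In the simulation of step 5 (share 0.565) it rose from 2.33 to 3.22 points, or 38%, slightly beyond that range.

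**The case against.** The case on the other side is substantial.

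- **The weakness is disclosed and was acted on.** Monitoring found the imbalance, the cut-off was changed, and the text explains why equal dosing was not possible. This stands. It limits the likely trial-wide size, although the first 160 remain in the intention-to-treat analysis.
- **The bias depends on behaviour.** The protocol says only that participants might take less of a larger dose, and both scripts tell them to keep to the amount. Days without NRT score 0% on any dose. This stands, and it is why every range above starts at zero.
- **Dose subgroups are planned.** Also true, and they would give some indication of a denominator effect. But they test whether the effect varies by dose, and their strata are formed after allocation by different rules, so they do not give a randomised comparison at equal dose.
- **No model is named, and a full analysis plan may supply one.** Partly stands. The same-dose comparison uses exactly the genotype and FTND data that the plan already intends to analyse. What can be faulted is the stated purpose: attributing a between-arm difference to variables that are balanced between arms.
- **The intention-to-treat comparison is framed as one of pragmatic policies.** This supports keeping it as primary. It does not answer the question about information at equal dose.

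**Conclusion.** The point holds in conditional form. If milligram intake does not rise in proportion to dose, an imbalance in higher-dose prescribing lowers the primary outcome in the arm with more such participants. In the first 160 this was the phenotype arm. With a 21 mg patch and 80 per arm assumed, the size is 0 to about 4 points at the interim imbalance. Trial-wide it is 0 to about 1 point if later recruitment is balanced, against the 7.5-point target. The upper ends assume full patch wear and no extra oral intake on the higher dose.

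A reader might infer that the dose imbalance mechanically favours the genotype arm and that the planned analysis cannot remove it. The documents do not support that, for three reasons. The bias vanishes under proportional intake. Its direction is shown only for the first 160 and could change after the new cut-off. And the genotype and FTND data, used differently, do allow a comparison free of the dose difference. The supported conclusion is narrower: the analysis as worded would not remove a dose effect, and the dose subgroups do not fill the gap.

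**What to change.** Keep the intention-to-treat t-test as the primary analysis and make these changes, all to the analysis only.

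1. Using genotype and FTND from both arms, and the FTND cut-off in force when each participant was randomised, derive the oral dose each participant would receive under each arm. Pre-specify the primary comparison among those with the same dose under both as a supporting analysis. The subset rests on characteristics fixed before randomisation, so the comparison within it remains randomised.
2. Report patch and oral adherence separately. The patch rule is the same in both arms, so patch adherence does not carry the oral denominator. Mean milligrams consumed is not a substitute, because it depends on dose in the opposite direction.
3. State that adjusting for genotype and phenotype alone does not address dose.

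The cost is precision and scope. About 55% to 71% of participants contribute (roughly 346 to 448 of 630, assuming genotype and FTND are independent), with a standard error about 19% to 35% larger. The result applies to that subset only. Participants whose genotyping fails drop out of it; the protocol expects a success rate above 95%.
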